### Random assignment and blinding

Following the baseline visit, a statistician off-site conducted the centralized, stratified block randomization of participants according to age, gender and baseline systolic blood pressure to maintain allocation concealment and to prevent selection bias. The identity of all participants who were randomized to receive the intervention was kept in a locked cabinet in the leading researcher's locked office according to university and hospital ethics approval. Data collection conducted by the research assistant was blinded to the intervention group. At the 9-month visit (T4), participants will be asked if they think they received standard care or the intervention or were unsure and why [34]. However, participants in the intervention group could not be blinded as the intervention was delivered face-to-face and it would be expected that this group would accurately guess their group assignment. Participants in either group received no remuneration for participation.

### Power analysis

We based our sample size on Gerin et al.'s [35] medication adherence and blood pressure control (ABC) research, using the standard deviation for systolic blood pressure of 12.1 mmHg cited in the usual care systolic blood pressure group. The sample size determined to allow the detection of a mean (± SD) difference in systolic blood pressure of 3-6 mmHg between the intervention and control groups. The sample size calculation has yielded 51 participants per group with 80% power (a = 0.05 [one-tailed], including 5% attrition, totalling 108 participants in all.

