**Methods:**

We developed a multifactorial intervention consisting of Self Blood Pressure Monitoring (SBPM), medication review, a twenty-minute interactive Digital Versatile Disc (DVD), and follow-up support telephone calls to help consumers improve their blood pressure control and take their medications as prescribed. The intervention is novel in that it has been developed from analysis of consumer and health professional views, and includes consumer video exemplars in the DVD. The primary outcome measure was a drop of 3-6 mmHg systolic blood pressure at three months after completion of the intervention. Secondary outcome measures included: assessment of medication adherence, medication self-efficacy and general wellbeing. Consumers' adherence to their prescribed medications was measured by manual pill count, self-report of medication adherence, and surrogate biochemical markers of disease control.

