### Study design

The study is a single-site, single-blind, longitudinal RCT. Participants have been allocated to one of two groups: the intervention group receives a multifactorial intervention designed to improve blood pressure control and medication adherence, and the control group receives standard care offered by the treating hospital's outpatient clinics and primary care provided by the participants' general practitioner. Data are collected at four time points: enrolment baseline data collection (T1), immediately following delivery of the intervention (T2), three months post-intervention (T3) and 9-months post-intervention (T4).

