### Data analysis

The analysis will be performed on an intent-to-treat basis. All data will be entered into an ACCESS database by a second research assistant who is blinded to the intervention group. An experienced biostatistician will check the integrity of the database and conduct statistical analyses. Descriptive statistics will be used to summarise demographic, social and medical data between the intervention and usual care groups and any effect of these variables on primary and secondary outcomes. Baseline characteristics of the intervention and usual care groups will be compared. Blood pressure, medication adherence, medication self-efficacy, and general wellbeing between the usual care and intervention groups will be compared to assess the effects of the intervention between groups and within participants at T2, 3 and 4 using t-tests as appropriate. The various measures of medication adherence will be examined for correlations. Continuous variables that are not normally distributed will be examined using equivalent non-parametric tests. Differences in change in binary categorical variables within each group will be analysed using McNemar's test and the changes between the two groups will be assessed by chi-squared tests for trends. Potential confounders may include comorbidities and number of prescribed medications. Statistical significance will be determined with p values of < 0.05.

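### The 80% power claimed for a 3-6 mmHg difference with 51 per group holds only at 6 mmHg; at 3 mmHg power is about 34%

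*Protocol article*

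**What the plan says.** The Power analysis section of the protocol article takes its variability from a cited adherence and blood pressure study: "standard deviation for systolic blood pressure of 12.1 mmHg cited in the usual care systolic blood pressure group". It says that the sample was chosen so that the trial could detect a mean "difference in systolic blood pressure of 3-6 mmHg between the intervention and control groups". The result follows: "The sample size calculation has yielded 51 participants per group with 80% power", at "a = 0.05 [one-tailed"], and then "including 5% attrition, totalling 108 participants in all". The section does not say which point of the 3-6 mmHg range entered the calculation.

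The abstract carries the same range into the endpoint: "The primary outcome measure was a drop of 3-6 mmHg systolic blood pressure at three months after completion of the intervention". The Data analysis section plans to compare the groups "using t-tests as appropriate". It sets the significance threshold at 0.05 without saying whether the tests are one- or two-sided. No baseline adjustment and no smaller change-score SD is mentioned as part of the sizing.

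**The concern.** For a fixed sample size, SD and alpha, power is an increasing function of the true difference. A single n can therefore meet 80% at only one difference, and every smaller difference has less. Stating one n and one power for a range whose ends differ by a factor of two leaves open which end was used. Because n scales with the inverse square of the difference, the two ends call for sample sizes that differ by a factor of four.

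What is at stake is the reading of a non-significant primary result. Someone told that the trial had 80% power for 3 mmHg would take such a result as fair evidence against a benefit of that size. If the power there is much lower, that inference is not justified.

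**Working it through.** **Inputs, all from the Power analysis section unless noted**

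- SD 12.1 mmHg, taken as common to both groups
- alpha 0.05, one-tailed
- power 80%
- difference 3-6 mmHg
- 51 per group; 5% attrition; 108 in total
- two groups (Study design section), taken as equal in size because one n per group is given
- two-sample t-test (Data analysis section)

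**Step 1: reproduce the stated figures**

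Normal approximation: n per group = 2 × [SD × (z₀.₉₅ + z₀.₈₀) / δ]².

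At δ = 6: 2 × [12.1 × (1.645 + 0.842) / 6]² ≈ 50.3, rounded up to 51. The t-test calculation gives 50.98, also 51.

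Attrition: 51 / 0.95 = 53.7, rounded up to 54 per group, and 2 × 54 = 108.

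Both stated figures reproduce exactly at 6 mmHg.

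**Step 2: sample size and power over the rest of the range**

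Standard error of the difference with 51 per group: 12.1 × √(2/51) = 2.40 mmHg. Approximate power = Φ(δ/2.40 − 1.645). For example, at 3 mmHg: Φ(1.25 − 1.645) = Φ(−0.39) ≈ 0.35.

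| True difference (mmHg) | n per group for 80% power (t-test, rounded up) | Power at 51 per group, t-test | Power at 51 per group, normal |
|---|---|---|---|
| 6 | 51 | 80.0% | 80.5% |
| 5.5 | 61 | 73.7% | 74.2% |
| 5 | 74 | 66.6% | 67.1% |
| 4.5 | 91 | 58.7% | 59.2% |
| 4 | 114 | 50.5% | 51.0% |
| 3 | 202 | 34.4% | 34.7% |

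By the normal approximation, the smallest difference with 80% power at 51 per group is (1.645 + 0.842) × 2.40 ≈ 5.96 mmHg. For 3 mmHg, 202 completers per group become 202 / 0.95 = 212.6, so 213 per group and 426 in total.

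**Step 3: does actual recruitment change this?**

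The Participant flow section reports 111 recruited. With 55 per group and nobody lost, t-test power at 3 mmHg is 36.2%.

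**Step 4: dependence on a one-tailed test**

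With a two-sided test at 0.05 and 51 per group, t-test power is 69.9% at 6 mmHg and 23.7% at 3 mmHg.

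**Step 5: what would rescue 3 mmHg with 51 per group?**

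- An SD of 3 / [√(2/51) × 2.487] ≈ 6.1 mmHg for the quantity compared, about half the stated value; or
- baseline adjustment with 1 − r² = 51 / 201.2 = 0.254, so r ≈ 0.86.

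The document states neither.

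**The case against.** The best defence is that the range is loose wording around a correct calculation. The figures of 51 and 108 are right for 6 mmHg, recruitment passed its target, and nothing in the design, endpoint or analysis changes. That much stands, and it limits the remedy to wording. It does not save the sentence, because this is the passage that justifies the sample size and it attaches 80% power to the whole range.

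A second defence is that baseline adjustment or a change score could raise power. It could, but only an SD near 6.1 mmHg or a correlation near 0.86 would be enough at 3 mmHg, and the document relies on neither.

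Several stronger readings are tempting, but the document does not support them:

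- **The attrition figures are wrong.** A reader might infer this because 2 × 51 = 102, not 108. The numbers agree once 51 is read as completers and 54 as randomised. The bracket in the sentence is never closed, and the attrition phrase attaches naturally to the total. This is a clarification only.
- **A true benefit of 3-4 mmHg would be missed more often than not.** At 4 mmHg power is 50.5%, an even chance. The statement holds only below about 4 mmHg.
- **A null result could not exclude 3 mmHg.** The two-sided 95% half-width is about 1.96 × 2.40 = 4.7 mmHg, so an estimate more than about 1.7 mmHg in the wrong direction would exclude it. With no true effect that happens in about 24% of trials. The interval that matches a one-tailed 5% test is the 90% one, with a half-width of about 3.9 mmHg.
- **The abstract declares 3 mmHg a success.** It names a range as the outcome measure but sets no success rule, and the first study hypothesis asks only for a greater reduction.
- **The SD is too small.** Nothing in the document points to a larger value. The SD at baseline would be a poor check, because the systolic entry threshold of 130 mmHg truncates that distribution.

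**Conclusion.** The power statement is wrong as written. On the plan's own inputs, 51 completers per group have 80% power at 6 mmHg and not at any smaller difference in the claimed range. Power falls to about 67% at 5 mmHg, 59% at 4.5, 51% at 4 and 34% at 3. A true 3 mmHg benefit would be missed about two times in three, and 80% power for it would need roughly four times as many completers (202 against 51 per group).

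This rests on an SD of 12.1 mmHg in both groups, equal allocation, an unadjusted two-sample t-test and a one-tailed 5% level. The last is the assumption most open to question, since the Data analysis section does not give the sidedness of the tests. Two-sided testing would lower the figures to about 70% at 6 mmHg and 24% at 3. The error lies in what the sentence claims; the sample size calculation at 6 mmHg is correct.

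**What to change.** Replace the sizing sentence in the Power analysis section with wording such as:

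> 51 completers per group (54 randomised per group, 108 in total, allowing 5% attrition) give 80% power to detect a difference of 6 mmHg (SD 12.1, one-tailed 5%); power is about 59% at 4.5 mmHg and 34% at 3 mmHg.

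Drop the claim that 3 mmHg is detectable with 80% power. State that a non-significant result will be interpreted from the confidence interval for the difference.

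Make the quoted figures match the test that will be used. If the final test is two-sided, give about 70% at 6 mmHg and 24% at 3 mmHg instead.

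The cost is wording only: no extra participants and no change to endpoint, allocation or analysis. The one drawback is that the stated power looks less favourable below 6 mmHg. The Data analysis section still describes the analysis as future work, so the correction can be made before results are interpreted.

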### Participant flow

Recruitment commenced on the 27th August 2008 and ceased on 17^th ^June 2009. A total of 111 participants were recruited and baseline data taken. The enrolment baseline visits commenced on the 8^th ^September 2008 and ceased on 22^nd ^June 2009. Participant flow is shown in Figure 1.

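### The one-tailed 5% alpha used to size the trial is not carried into the analysis section or justified; tested two-sided, power at 6 mmHg is about 70%

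*Protocol article*

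**What the plan says.** The Power analysis section takes its SD from an earlier adherence and blood pressure study, "using the standard deviation for systolic blood pressure of 12.1 mmHg cited in the usual care systolic blood pressure group". It aims to detect a "difference in systolic blood pressure of 3-6 mmHg between the intervention and control groups" and reports that "The sample size calculation has yielded 51 participants per group with 80% power". It then gives the error rate and the total: "80% power (a = 0.05 [one-tailed], including 5% attrition, totalling 108 participants in all". This is the only place where the article names the number of tails.

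The Data analysis section compares the groups at T2, T3 and T4 with t-tests or their non-parametric equivalents, and uses McNemar's test and chi-squared tests for binary variables. One criterion covers all of them: "Statistical significance will be determined with p values of < 0.05". Sidedness is not mentioned.

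The Study hypotheses section words hypothesis 1 directionally: the intervention group is expected to have the greater fall in blood pressure at T3. It gives no alpha and no number of tails. Under Participant flow, "A total of 111 participants were recruited and baseline data taken".

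**The concern.** A sample size calculation supports the planned test only if both use the same error rate. Here the sizing is explicit (one-tailed, 5%) and the analysis is not. A bare threshold of 0.05, applied to t-tests, McNemar's test and chi-squared tests alike, would ordinarily be read as two-sided, and standard software reports two-sided p values unless told otherwise. On that reading the trial has less power than stated. On the other reading, the primary claim rests on a one-tailed 5% test, and the article does not say why a rise in blood pressure under the intervention need not be distinguished from no effect.

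What is at stake is the primary conclusion when the result is borderline. If the observed difference favours the intervention with a two-sided p between 0.05 and 0.10, one rule calls the trial positive and the other does not. While the rule is open, it could be settled after the data are seen.

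**Working it through.** **Inputs, all from the Power analysis section.** SD σ = 12.1 mmHg; difference δ = 6 mmHg (the upper end of the stated range, and the end that yields 51 per group); power 80%; α = 0.05 one-tailed; attrition 5%. Equal groups are implied by 51 per group.

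**Step 1: reproduce the stated size.** n per group = 2σ²(z_α + z_β)² / δ².

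- One-tailed: 2 × 146.41 × (1.645 + 0.842)² / 36 = 50.3, rounded up to 51. The exact noncentral t calculation also gives 51.
- Attrition: 51 / 0.95 = 53.7, rounded up to 54 per group, or 108 in total.

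Both printed figures reproduce.

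**Step 2: power at 6 mmHg with 51 per group.** The standard error of the difference is 12.1 × √(2/51) = 2.396 mmHg, so δ/SE = 2.504.

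- One-tailed 5%: Φ(2.504 − 1.645) = 80.5% by the normal approximation; 80.0% by noncentral t.
- Two-sided 5%: Φ(2.504 − 1.960) = 70.7% by the normal approximation; 69.8% by noncentral t.

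The cost of moving to two-sided testing is therefore about 10 percentage points.

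**Step 3: difference detectable with 80% power, 51 per group.** (z_α + z_β) × SE.

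- One-tailed: 2.487 × 2.396 = 5.96 mmHg (6.00 by noncentral t).
- Two-sided: 2.802 × 2.396 = 6.71 mmHg (6.78 by noncentral t).

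**Step 4: size needed for two-sided 80% power at 6 mmHg.** 2 × 146.41 × (1.960 + 0.842)² / 36 = 63.8, so 64 per group (65 by noncentral t). With 5% attrition this is 68 per group, or 136 in total.

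**Step 5: does actual recruitment close the gap?** With all 111 participants evaluable (55.5 per group on average), two-sided power at 6 mmHg is about 73.5% by noncentral t. After 5% loss, 111 × 0.95 ≈ 105 remain and power is about 71%. The gap remains.

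**Step 6: where the two rules disagree.** With 100 degrees of freedom the critical t values are 1.660 (one-tailed) and 1.984 (two-sided). Multiplied by 2.396, they put the smallest significant observed difference at 3.98 and 4.75 mmHg. An observed advantage between about 4.0 and 4.75 mmHg is significant under one rule and not under the other. That band lies inside the article's own 3–6 mmHg target range.

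**The case against.** The strongest reply is that the two sections do not contradict each other. The analysis section never says two-sided, and a one-tailed p below 0.05 satisfies both statements. The directional hypotheses fit the one-tailed sizing. The one-tailed alpha is openly printed, and a condensed article may leave the sidedness of each test to the full protocol or the statistical analysis plan.

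Much of this stands. A reader might infer that the stated 80% is a calculation error, or that the article commits to two-sided testing and so contradicts itself. The document supports neither: 51 and 108 are right for the one-tailed inputs, and 70% is the power of a test that the article does not expressly adopt.

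The reply does not remove the point. A directional hypothesis says what is expected; it neither fixes the alpha of the test nor explains why harm can be disregarded. The article itself prints an explicit one-tailed alpha in one section and an unqualified threshold in another, so the two statements need to be aligned wherever the remaining detail sits. A justified one-tailed 5% test, written into the analysis section, would also remove the ambiguity, but it would keep the 5% false-benefit rate. The 2.5% benchmark is convention and is not set by this document.

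**Conclusion.** The point holds as an unresolved decision rule, not as an arithmetic mistake. If the primary T3 comparison is two-sided at 5%, power at 6 mmHg is about 70% instead of the stated 80%, and 80% power applies to about 6.8 mmHg. If it is one-tailed at 5%, the power is as stated, and the false-benefit rate is 5% against the conventional 2.5%, without a reason given.

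These figures assume a two-sample t-test on systolic pressure, SD 12.1 mmHg, 51 completers per group and a true difference of 6 mmHg. Low power towards the 3 mmHg end of the target range should not be charged to sidedness: at 3 mmHg it is only about 34% even one-tailed. That comes mainly from stating the target as a range, which is a separate matter.

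This should be fixed before analysis. It does not invalidate the design: the one-tailed assumption is published, and the conclusion would change only for borderline results.

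**What to change.** In the Data analysis section, state that the primary comparison of systolic blood pressure at T3 is tested two-sided at the 5% level and reported with a 95% confidence interval. In the Power analysis section, restate that 51 completers per group give about 70% power for a 6 mmHg difference, or 80% power for about 6.8 mmHg, at SD 12.1 mmHg.

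Both changes should be made and dated before the analysis. The article describes the analysis in the future tense and projects follow-up to July 2010, so on its own account there was still time. The cost is one sentence in each section and a less favourable stated power. No further recruitment is needed.

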### Participant flow

Recruitment commenced on the 27th August 2008 and ceased on 17^th ^June 2009. A total of 111 participants were recruited and baseline data taken. The enrolment baseline visits commenced on the 8^th ^September 2008 and ceased on 22^nd ^June 2009. Participant flow is shown in Figure 1.

**Figure 1 F1:**
[figure not shown]
**Trial participant flow**.

### Data analysis

The analysis will be performed on an intent-to-treat basis. All data will be entered into an ACCESS database by a second research assistant who is blinded to the intervention group. An experienced biostatistician will check the integrity of the database and conduct statistical analyses. Descriptive statistics will be used to summarise demographic, social and medical data between the intervention and usual care groups and any effect of these variables on primary and secondary outcomes. Baseline characteristics of the intervention and usual care groups will be compared. Blood pressure, medication adherence, medication self-efficacy, and general wellbeing between the usual care and intervention groups will be compared to assess the effects of the intervention between groups and within participants at T2, 3 and 4 using t-tests as appropriate. The various measures of medication adherence will be examined for correlations. Continuous variables that are not normally distributed will be examined using equivalent non-parametric tests. Differences in change in binary categorical variables within each group will be analysed using McNemar's test and the changes between the two groups will be assessed by chi-squared tests for trends. Potential confounders may include comorbidities and number of prescribed medications. Statistical significance will be determined with p values of < 0.05.

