### Study hypotheses

1. Compared to participants receiving standard care, participants with diabetes and chronic kidney disease who receive the intervention will show greater reduction in blood pressure at three months post-intervention (T3).

2. Compared to participants receiving standard care, participants with diabetes and chronic kidney disease who receive the intervention will show a greater adherence to their prescribed medication regimen at three months post-intervention (T3).

3. Improved medication adherence will be associated with increased systolic blood pressure control at three months post-intervention (T3).

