### Enrolment and randomization

Participants who expressed an interest in participating and who met the inclusion criteria were contacted by the research assistant by telephone to organize a home visit. At the home visit, formal informed consent was obtained prior to collecting demographic, social and medical data, sitting blood pressure according to accepted guidelines [17] (taken twice on the arm with the lowest reading a minute apart and averaged), body mass index, comorbidity burden, baseline surveys and pill counts (Table 2). The baseline visits lasted approximately 1 1/4 hours each.

**Table 2 T2:** Schedule of data collected from consumers at each data collection point

Measures	T1	T2	T3	T4
Demographics(age, gender, education, usual role, social support)	X			
English proficiency	X			
Abbreviated mental health test	X			
Chronic conditions	X			
Prescribed medications	X			
Body Mass Index	X			X
Blood pressure	X	X	X	X
SF-12v2-Item Health Survey	X	X	X	X
MASES Self-Efficacy Scale	X	X	X	X
Morisky scale	X	X	X	X
Health care utilisation scale	X	X	X	X
Pill count	X	X	X	X
Serum & urine laboratory measures ie eGFR, urine Malb/Cr ratios, creatinine, Hb, HbA_1C_, CaPO4, lipids	X	X	X	X

All participants have data collected at four points in time (Table 2): baseline (T1), 3-month following the baseline data collection and at completion of the intervention (T2), and 6- (T3) and 9-months (T4) post-intervention (12-months post-baseline data collection). Routine clinical laboratory surrogate measures indicative of medication adherence taken as part of the participant's standard treatment such as eGFR, urine microalbumin/creatinine ratios, serum creatinine, Hb, Hb A_1C_, CaP04 and low-density lipids are collected at these four time points from the participant's medical records. Follow-up is projected to continue until July 2010.

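### The t-tests planned for systolic pressure make no adjustment for the randomisation factors: valid, but less powerful at T3 than a baseline-adjusted analysis

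*Protocol article*

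**What the plan says.** The Data analysis section sets the method for blood pressure, medication adherence, self-efficacy and wellbeing: these "will be compared to assess the effects of the intervention between groups and within participants at T2, 3 and 4 using t-tests as appropriate". Non-parametric equivalents are foreseen for non-normal variables. On covariates it adds: "Potential confounders may include comorbidities and number of prescribed medications". It also promises descriptive statistics on any influence of demographic, social and medical variables on the outcomes.

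The Random assignment and blinding section describes "stratified block randomization of participants according to age, gender and baseline systolic blood pressure". Baseline pressure is available for everyone enrolled: at the home visit it was "taken twice on the arm with the lowest reading a minute apart and averaged". Table 2 lists age and gender among the baseline data.

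The primary time point is T3. The abstract states: "The primary outcome measure was a drop of 3-6 mmHg systolic blood pressure at three months after completion of the intervention". Hypothesis 1 says that the intervention group "will show greater reduction in blood pressure at three months post-intervention (T3"). The Power analysis section sizes the trial "using the standard deviation for systolic blood pressure of 12.1 mmHg cited in the usual care systolic blood pressure group", for a "difference in systolic blood pressure of 3-6 mmHg between the intervention and control groups", one-tailed at 0.05 with 80% power.

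**The concern.** The design spends effort on balancing baseline systolic pressure, age and gender, but the stated analysis has no term for any of them. Two consequences follow.

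- **Lost precision.** Baseline pressure normally predicts later pressure. A t-test on the T3 value leaves that predictable variation in the error term. A t-test on change removes it with a fixed slope of 1, which over-corrects whenever the correlation is below 1 (equal variances at the two visits).
- **Conservatism.** Stratification makes the arms more alike at baseline than simple randomisation would. A t-test on the T3 value does not credit this, so its standard error is too large and its true size falls below the nominal level.

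This matters because the trial has little power to spare. The stated sample size gives 80% only at the top of the 3-6 mmHg range and only one-tailed. Recruitment closed at 111, so the analysis is the place where precision can still be gained.

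**Working it through.** **Inputs.** From the Power analysis section: SD 12.1 mmHg, difference 6 mmHg (upper end of the range), 51 per group, alpha 0.05 one-tailed, 80% power, 5% attrition. Assumed, because the documents do not give it: baseline-T3 correlation ρ of 0.3, 0.5 or 0.7, with equal variances at the two visits.

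**1. The plan's own figure.** n per group = 2 × (1.645 + 0.842)² × 12.1² / 6² = 50.3, so 51. With attrition, 51 / 0.95 = 53.7, so 54 per group and 108 in all. The stated size reproduces, and it is an unadjusted two-mean calculation. Two-sided at 6 mmHg it would be 64 per group; one-tailed at 3 mmHg, 202.

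**2. SD under each analysis.**
- T3 value: 12.1
- Change: 12.1 × √(2(1 − ρ)) = 14.32, 12.10, 9.37
- ANCOVA: 12.1 × √(1 − ρ²) = 11.54, 10.48, 8.64

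The ANCOVA variance is 1 − ρ² = 91%, 75%, 51% of that for the T3 value, and (1 + ρ)/2 = 65%, 75%, 85% of that for change. It is smaller than both at every ρ assumed.

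**3. Power at 6 mmHg, 51 per group.** The standard error is SD × √(2/51). For the T3 value it is 2.396, giving a noncentrality of 6 / 2.396 = 2.504. The other analyses scale this by 12.1/SD. Power is from the noncentral t distribution with 100 degrees of freedom.

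| Analysis | One-tailed, ρ 0.3 / 0.5 / 0.7 | Two-sided, ρ 0.3 / 0.5 / 0.7 |
|---|---|---|
| t-test, T3 value | 80% at each | 70% at each |
| t-test, change | 68 / 80 / 94% | 55 / 70 / 89% |
| ANCOVA on baseline | 83 / 89 / 97% | 74 / 82 / 94% |

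By the normal approximation, the number per group for 80% one-tailed power falls from 51 to 46, 38 or 26 with ANCOVA.

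**4. True size of the T3-value t-test.** Simulation with no treatment effect: 102 patients, two baseline-pressure strata split at the median, near-equal allocation within each, 8,000 replicates per ρ. The nominal two-sided 5% test rejected in about 4.5%, 3.3% and 2.0% of trials at ρ 0.3, 0.5 and 0.7. With a 6 mmHg effect the same test had power of about 71%, 72% and 73%. Stratification alone therefore recovers little of what adjustment offers.

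**5. If 12.1 is the SD of change.** The ANCOVA SD becomes 12.1 × √((1 + ρ)/2) = 9.76, 10.48, 11.16. One-tailed power is about 93%, 89% and 85%, against 80% for the change t-test. The direction is the same.

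**6. Lower end of the range.** At 3 mmHg one-tailed, power is about 34-35% unadjusted and 37% to 54% with ANCOVA. Adjustment does not rescue that end.

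**The case against.** The strongest reply is that nothing is invalid. A t-test in a randomised trial is unbiased, it does not exceed its nominal size at T3, and the sample size was computed for exactly that test. This stands, and it limits the point to efficiency.

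The size of the gain is also uncertain. Entry required a systolic pressure of at least 130 mmHg, which narrows the baseline range and tends to lower the correlation; at 0.3 the gain over a T3-value t-test is only 3-4 points. A separate analysis plan may add covariates, and the descriptive look at demographic influences could touch age and gender. Even so, the method that this document names is the t-test.

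A reader might infer more than the documents support:

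- **Baseline is ignored altogether.** Hypothesis 1 speaks of reduction, and the analysis text mentions within-participant effects, so the test may be on change. That would use baseline pressure, only less efficiently.
- **Three visits mean three chances to win.** The abstract and hypothesis 1 both place the primary outcome at T3, and nothing lets T2 or T4 count as success. A family-wise error claim has no basis here, and calculating one at full 5% size per test would also conflict with the conservatism shown above.
- **The true size is lower still.** That requires perfect balance on continuous pressure. Stratified blocks balance categories only, and the cut-points are not given.
- **Patients missing a visit are dropped despite intention to treat.** The article does not say so, and missing-data handling may properly sit in the analysis plan.
- **The two-sided 70% is caused by the t-test.** It comes from sidedness; on the planned one-tailed test the power is the intended 80%.

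**Conclusion.** The point holds as one of efficiency. The stated t-tests leave out the factors that randomisation was stratified on, and they have less power than ANCOVA whether applied to the T3 value or to change. At 6 mmHg and 51 per group, baseline adjustment lifts one-tailed power over a T3-value t-test by about 3, 9 or 17 percentage points at correlation 0.3, 0.5 or 0.7. Over a change-score t-test the gain is about 15, 9 or 3 points. These figures rest on an assumed correlation, equal variances and 12.1 mmHg being the SD of the pressure level. They count baseline pressure alone; no figure is claimed for age and gender. There is no finding of bias or of inflated type I error. The change is worth making because it is nearly free, but the trial is not unsound without it.

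**What to change.** Name one primary analysis of systolic pressure at T3: an ANCOVA, or a mixed model for repeated measures over T2 to T4 with the T3 arm contrast as primary. Include continuous baseline systolic pressure, age and gender as fixed covariates. Report the adjusted arm difference with a confidence interval, and state whether the test is one- or two-sided, since the Power analysis section is one-tailed and the Data analysis section is silent. Treat T2 and T4 as supportive. Use the same baseline-adjusted form for the continuous secondary outcomes. Present comorbidities and number of medications, if wanted, as a separate sensitivity analysis.

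The cost is analysis wording only: every covariate is already collected and no patient, visit or measurement is added. The change should be fixed before outcome data are seen by arm. The Enrolment and randomization section describes the timing of T3 differently from the Study design section and the hypotheses; this separate discrepancy should be reconciled so that the primary contrast refers to one defined visit.
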